#### Interim analyses

Interim analyses will be performed after the completion of the second measurement point (t1) to evaluate the intervention program’s effectiveness in terms of the primary outcome. The second measurement point is expected to be completed in June 2025. These interim analyses are particularly relevant for the annual reports that the research team provides to the project funder. The study will not be modified or terminated based on interim analyses.

### Ethical considerations

#### Protocol amendments

All major changes to the study protocol that may affect the conduct of the study, intervention design, outcomes, or participant safety will be submitted as an amendment to the respective ethics committee of the involved research institutions for approval and subsequently communicated by the project coordination to all relevant parties through regular planning meetings, direct contact, and newsletters. The registration with the German Clinical Trials Registry (DRKS00029002) will be updated according to amendments. This study protocol is the second major version (27 March 2023).

#### Adverse events

We consider the risk of adverse effects from participating in the study’s data collection to be low, apart from potentially short-term discomfort of participants while reporting and discussing their unemployment and psychological well-being.

Participation in the intervention program will be voluntary and can be paused or terminated at all times during the 12-months intervention phase. The intervention program is explicitly aimed at supporting participants’ re-employment and mental health recovery so we consider the risk of adverse effects through participation to be low. Research staff and intervention providers will continuously monitor for serious adverse events. Any serious adverse events will be discussed in regularly scheduled clinical supervision sessions and their occurrence will be documented in the session records. Furthermore, participants are provided with contact details of research staff to report adverse events. Research staff and intervention providers are provided with clear guidelines if participants were to express thoughts and plans of self-harm. As we consider the risk of adverse effects of intervention participation to be low, we will conduct regular data monitoring internally; no independent data monitoring committee will be formed.

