Upon study entry, research staff will record detailed contact information from participants as well as their banking details for compensation, including written consent to use these details for said purpose. Subsequently, research staff will conduct an entry interview with participants and ask them to complete a questionnaire (i.e., baseline assessment, t0). After completing this baseline assessment, participants will be contacted for a short telephone interview after six months to assess health service utilization in the preceding six months, as well as after 12 months (i.e., t1) and 18 months (i.e., t2) for more in-depth assessment similar to the baseline assessment, including conducting an interview and completing a questionnaire. Additionally, research staff will ask participants’ written consent to request certain data from their job center records, specifically their status of receiving basic income support benefits (yes vs. no) and the duration of receiving full basic income support at 12, 18 and 24 months after study entry. Whether written consent for this additional data request is given or not will not affect study participation.

Figure 1 shows a flow chart for participants’ study experience.

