
Each local intervention team will include an 80% FTE job coach. All job coaches will work manual-based [55]. They will receive an online training course (https://ipsworks.org/index.php/training-courses/) and a one-day, in-person training course from a German expert in IPS job coaching as well as participate in workplace shadowing in an established IPS unit. Throughout the intervention, they will receive weekly group supervision and individual supervision if needed. Supervision is provided by the same project-internal individuals that provide supervision to the other components. Additionally, job coaches will receive a monthly supervision session by the aforementioned IPS expert external to the team.

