#### Adherence and auditing

Participants can determine which components they use, in what combination and for how long over the 12-months intervention phase. Intervention providers will offer participants regular appointments (i.e., every one to two weeks) with low-threshold scheduling to enable regularity and structure. Although face-to-face appointments are preferred, also in terms if relationship building, intervention providers will offer online appointments as well where necessary. To facilitate face-to-face appointments, reimbursement of travel costs is offered.

Participating in a component can be paused or terminated within the time frame of the 12-months intervention phase. If participants state they would like to pause or terminate participation in one component, intervention providers will stress that the access to that component remains open within the 12-months period and encourage participants to contact intervention providers if their needs change and they would like to resume the component. Additionally, intervention providers will continuously encourage participation in the other two components where considered beneficial. If participants do not use any component for a certain time, research staff will regularly contact them to offer support via the intervention, potentially re-iterating the intervention components.

The intervention providers’ conduct and adherence to intervention manuals will be discussed in regular supervision meetings. Furthermore, every six months, there will be a fidelity assessment for each intervention component to review and, if necessary, further develop high fidelity in each component. The fidelity assessment will be conducted by an internal and an external reviewer based on predefined fidelity scales. Subsequent fidelity reports and emerging barriers will be discussed with the principal investigators and measures taken to improve intervention fidelity further if required.

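### Serious adverse events are documented through supervision described only for the intervention's providers, so ascertainment is unequal and recorded counts cannot be compared between groups

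*Protocol article*

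**What the plan says.** The Adverse events section sets out how harm is watched for. Detection is shared: "Research staff and intervention providers will continuously monitor for serious adverse events". In addition, "participants are provided with contact details of research staff to report adverse events", with no restriction to one group. For recording, one place is named: "Any serious adverse events will be discussed in regularly scheduled clinical supervision sessions and their occurrence will be documented in the session records".

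Supervision is described in the sections on the three components, and there it concerns the people who deliver them. For job coaches, for example, "Throughout the intervention, they will receive weekly group supervision and individual supervision if needed". The Short-term psychotherapy and Peer support sections say the same for their providers. Under Design and setting, the control group is passive and receives treatment as usual only.

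On contact, the Adherence and auditing section says of the intervention group: "Intervention providers will offer participants regular appointments (i.e., every one to two weeks) with low-threshold scheduling". For all participants, the Participant recruitment and timeline section says that "participants will be contacted for a short telephone interview after six months to assess health service utilization in the preceding six months", followed by fuller assessments at 12 months (t1) and 18 months (t2).

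The low-risk judgement is reasoned from the program's purpose: "The intervention program is explicitly aimed at supporting participants’ re-employment and mental health recovery so we consider the risk of adverse effects through participation to" (the sentence closes by calling that risk low). That judgement is then the ground for the oversight arrangement: "we will conduct regular data monitoring internally; no independent data monitoring committee will be formed".

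**The concern.** A harm record can be compared between groups only if both are asked about harm in the same way and equally often. Here the named record belongs to a process that, as far as it is described, exists for one group only. That group is also seen much more often for 12 months. SAE counts would then partly reflect how often someone was in a position to hear of an event.

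Two things are at stake. If the risk is the same in both groups, the intervention group may appear to have more events. If the program in fact prevents serious events, the same imbalance may hide it. Either way, the untreated cohort that the trial follows with the same interviews would be of no use for checking the low-risk judgement, although it could serve that purpose at little cost. The team intends to publish its findings and to promote the program as a regular job center service, so a usable statement on harm has practical value.

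**Working it through.** The article gives no SAE figure to reproduce, so the check sets its sections side by side.

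**Step 1. Routes by which an SAE can be noticed and recorded.**

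| Route | Intervention group | Control group | Section |
|---|---|---|---|
| Monitoring by providers | yes | no providers | Adverse events; Design and setting |
| Monitoring by research staff | yes | yes | Adverse events |
| Participant reports to research staff | yes | yes | Adverse events |
| Weekly team meetings of researcher and providers, where cases are discussed | yes | no counterpart described | Integration of components |
| Research staff contact those using no component for a time | yes | no counterpart described | Adherence and auditing |
| Contact to keep contact details current | yes | yes, no safety question stated | Statistical methods |
| SAE question at a scheduled assessment | none listed | none listed | Table 2 |
| Documentation in supervision records | supervision of its providers described | no route described | Adverse events; component sections |

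The common routes are passive or unspecified. The additional routes all lie on the intervention side.

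**Step 2. Contact in the first 12 months after baseline.**

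- Both groups: the 6-month telephone interview and t1, so 1 + 1 = 2 scheduled follow-up assessments.
- Intervention group, psychotherapy: at most 10 regular plus 3 booster sessions, 10 + 3 = 13.
- Intervention group, job coaching: up to 25 hours before employment, unlimited within the 12 months afterwards.
- Intervention group, peer support: unlimited. At one appointment every one to two weeks, 52 / 2 = 26 to 52 / 1 = 52 appointments if every offer were taken up.

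The range of 26 to 52 must not be applied to every component, because psychotherapy is capped well below it and coaching before employment is limited in hours. Components are also voluntary, so actual contact will vary widely between participants. The contrast in offered contact with two scheduled assessments remains.

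**Step 3. What unequal capture does to a ratio.** Let p be the true SAE risk, equal in both groups, and let s be the share of events that is recorded. The apparent ratio is

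(p × s_IG) / (p × s_CG) = s_IG / s_CG.

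The true risk cancels, and only the ratio of the capture shares matters. The article gives neither p nor s. Purely as an assumption, if control capture were 75%, 50% or 25% of intervention capture, the apparent ratio would be 1 / 0.75 = 1.33, 1 / 0.50 = 2.0 or 1 / 0.25 = 4.0. Nothing in the document favours any of these values. They show only that the range is wide.

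**Step 4. Time.** Provider contact ends at month 12, while both groups are followed to month 18. The imbalance therefore belongs to the intervention period, and capture within the intervention group also changes at month 12.

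**The case against.** The case on the other side is substantial, and most of it stands as a limit on the point.

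- A reader might infer that SAEs are found only through supervision. The text does not say so. Research staff, who carry out data collection in both groups, also monitor, and any participant may report to them. Supervision is where events are discussed and documented.
- A reader might infer that control-group events go unrecorded. No group is excluded from the session records, and the supervisors belong to the research project team. The article simply describes no route by which a control event reaches those records.
- A reader might infer that the trial will report a false risk ratio. None of Hypotheses 1 to 9, and nothing under Statistical methods, compares SAE counts between groups, so no planned analysis is biased.
- A reader might infer that harm cannot be examined at all. Both groups complete distress, depression, anxiety and somatic symptom scales at t1 and t2, and report health service use every six months. Worsening symptoms are thus measured alike in both groups, and the intervention group's own records can still describe its events.
- The article is condensed, and the full protocol may contain SAE forms. That is why the point is not that a form is missing. It rests on the recording rule that the article does state.

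What remains is that the stated rule ties documentation to supervision described for one group only, contact is unequal, and no common safety question is listed.

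**Conclusion.** The point holds in limited form. Followed as written, the plan ascertains SAEs unequally by group during the 12-month intervention. Recorded counts therefore cannot be compared between groups and cannot serve, by comparison, to back the low-risk judgement behind internal-only monitoring.

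The size of the distortion cannot be computed, because the article states neither an SAE rate nor a capture rate. The likely direction is over-recording in the intervention group relative to the control group. That rests on the assumption that more contact means more events noticed.

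The conclusion also assumes that the clinical supervision sessions in the Adverse events section are those described for the component providers, since the article describes no others. It does not rest on control events being excluded, or on any SAE comparison being planned. This is an inexpensive improvement to a stated rule and leaves the primary analysis untouched.

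**What to change.** Change the documentation rule in the Adverse events section:

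1. Put the same short, fixed set of SAE questions to both groups in the interviews already scheduled at 6, 12 (t1) and 18 (t2) months, each covering the time since the previous interview. Enter the answers in the study database.
2. Base any between-group statement on harm only on this common source, supplemented by the health service utilization data already collected from both groups every six months. The article does not say which serious events those data would reveal, so their use for this purpose should be spelled out.
3. Keep events learned through providers as a separate listing for the intervention group, not compared with the control group.

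The cost is one short database form and a few minutes per interview, with no new visits. There are two downsides. Recall error is possible and may differ by group, since intervention participants discuss their situation with providers. And because the control group is recruited first and recruitment was already under way when the manuscript was submitted, some control participants may be past their interviews. For them only the existing service-use data can serve, and the comparison must be limited to periods in which both groups were asked.

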#### Confidentiality

The collection, storage, and analysis of study data will be carried out in strict compliance with the General Data Protection Regulation of the European Union (DSGVO). Study data will be entered and stored in the project’s database secuTrial^®^ (interActive Systems Berlin). This database is password-protected both for participants and researchers and provides an audit trail. It is certified according to the guidelines for Good Clinical Practice of the International Council for Harmonization of Technical Requirements for Pharmaceuticals for Human Use. Each participant will be allocated a pseudonym (project-ID) by the database that allows us to connect study data from the various measurement points. The documents that connect personal data (e.g., contact details) with project-IDs will be password-protected and stored separately from the study data. Accordingly, datasets extracted from the database will be analyzed in a strictly pseudonymous form. Results will be published in anonymous and aggregated form. After project completion, data will be archived on servers of the two involved research institutions. Data which are collected on paper (e.g., interviews notes, signed consent forms, bank detail for compensation) will be stored separately form the study data in secure locations. All data related to the study will be stored securely by the involved research institutions for 10 years after study completion and subsequently deleted or destroyed. Digital data will be stored within the server infrastructure of the research institutions; physical data (e.g., signed consent forms) in locked file cabinets in areas with limited access.

Datasets that are extracted from the database will be password-protected and accessible only to the study’s biometrical experts within the research team, principal investigators, and the project coordination, as well as to research staff who express a legitimate interest in the data for further academic qualification and will have signed a data use agreement.

### Dissemination

The research team will publish all findings regarding the intervention’s effectiveness, implementation, and sustainability as permanent service in job centers via multiple pathways—independently from the funder, sponsor, or the collaborating job centers and regardless of strength and direction of the effects, including non-significant findings. The findings will be published in peer-reviewed scientific journals and presented at relevant national and international conferences. Authorship eligibility will be based on the recommendations outlined by the International Committee for Medical Journal Editors (ICMJE).

The funder will receive regular reports regarding project progress, including interim and final findings. Participants and staff of collaborating job centers will be informed about the study’s final findings through newsletters and an executive summary; this executive summary will also be published on the project’s public website (https://www.projekt-3for1.de). Additionally, findings will be disseminated as press releases to various media outlets. We will approach political decision-makers, multiplier institutions (e.g., Federal Employment Agency, chambers of industry and commerce, community psychiatric associations), and interest groups (e.g., non-profit organizations for individuals with lived experience) with the findings.

## Discussion

Unemployment incurs large costs for social welfare states and is detrimental to those affected, making it a significant public health concern. Unemployed individuals with mental health issues—partially as result of their unemployment—often desire to re-enter the labor market, but struggle to do so, experiencing multiple barriers. This is where the 3for1-project comes in, offering a multi-level support program that addresses both re-employment and mental health recovery in German job centers. By offering support on different levels, the proposed program fills an important gap in both research into unemployment and mental health, as well as in practice in job centers who are tasked to facilitate re-employment of basic income support recipients.

Our study has several strengths. One strength is that our intervention program addresses multiple areas of life that impede unemployed individuals with mental health issues from finding re-employment: obtaining and retaining employment, improving mental health, facilitating self-efficacy and self-determination, increasing social networks and activation level in daily life. The intervention program offers highly individualized support over a 12-months period to a high-risk population with complex needs for assistance. Furthermore, we will be able to compare the IG with a CG from the same population over multiple measurement points, including a 6-months follow-up assessment. Another strength is the recruitment of a substantial sample from six collaborating job centers—with some job centers being responsible for a city, others for partially rural districts. This design enhances the reliability and generalizability of the study’s findings.

Despite the innovative and comprehensive approach of our intervention program, our study has certain limitations. Firstly, the study groups are not randomized, but allocated based on time. As the 3for1-intervention program includes active cooperation with the job centers’ employment advisors, we expect that the culture and way of working in the job centers themselves could be changed by the intervention. Therefore, a parallel CG could be biased by these changes, impeding the evaluation of the intervention’s actual effectiveness. However, the non-randomization could mean that the two groups differ on demographic variables and relevant outcomes at baseline. Additionally, as the recruitment phase for both groups will cover several years, there may be various developments in society and policies that could affect the two groups differently. We will collect a variety of covariates and use analysis methods that enable us to control for these covariates, such as logistic regression or analysis of covariance, to minimize bias in the estimation of the intervention effect [99]. Another challenge will be participant retention across the 1.5-year study period. If participants drop out of the study, conclusions from the analysis might be biased by selective dropout (e.g., less motivated participants, participants in CG without offered benefit of the intervention program). As described, we will make every reasonable effort to collect data from as many participants as possible across the study period. Additionally, we will analyze the data in terms of selective dropout effects. Finally, insufficient German language skills are an exclusion criterion. Consequently, the effectiveness of the intervention program can only be evaluated for a subsample of unemployed individuals with mental health issues. Therefore, we can only draw limited conclusions about its broader effectiveness for job center clients with mental health issues in general.

Despite certain challenges of our study design, the 3for1-intervention program has great potential to be a valuable addition to the German job center infrastructure, offering support for a vulnerable group with a high need for assistance. Particularly, with the K6, job centers would be equipped with a reliable, quick and easy-to-use screening tool to identify this group. As part of the project, we will have implemented relevant administrative infrastructure within the job centers and deduced multiple best practices for implementation. These aspects will be invaluable in facilitating the sustainability of the intervention program within the job centers as a regular support offer for clients with mental health issues.

